### Research question

First, we want to find out how the cognitive, social, and mental health functions of refugee children compare with (a) same aged immigrant children without refugee background and (b) native-born children in Finland. We will also examine whether worse mental health (trauma-related and depressive symptoms) is linked with poorer cognitive function and social competence across the sample. We hypothesize based on earlier (limited) literature in the field, 1) that refugee children, for whom exposure to trauma is likely more common, exhibit lower levels of cognitive functioning compared to immigrant children without refugee background and native Finnish children, and 2) that mental health problems and poorer social competence explain this link.

Second, we will examine whether reliable evaluation of cognitive, social, and mental health functions of students can inform schools about supportive actions for refugee children and whether this process is different compared with non-refugee immigrant children and/or native-born Finnish children. We will look at whether children who scored above/under critical thresholds on our Screening Battery (SB) report receive supportive actions during the school year. If they do, we look at what kinds of actions inside and outside the classroom schools conduct for refugee children, and whether the output of the SB was utilized to plan this support We will further look at whether the actions are different compared to actions with non-refugee immigrant children and/or native-born Finnish children and whether the actions are different compared to actions that do not use the information produced by the screening battery.

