We will also examine whether the supportive actions are reflected in cognitive, social, and mental health functions of refugee children within their first year in Finnish schools (after controlling for other significant life changes during the study year). We will investigate whether this effect is different compared to non-refugee immigrant children and/or native-born Finnish children and if the effect is different compared to actions not using the information produced by the screening battery. We hypothesize 3) that supportive actions informed by the findings of the screening battery have a stronger positive effect than other actions. Finally, we will examine whether improvements in mental health (trauma, depression, resilience) and social functioning during the school year are associated with better performance in cognitive tests.

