### Feedback tool

The feedback tool collates information on participants’ cognitive, social, and mental health functioning and compiles two reports: one for the teacher and one for school health staff. The teacher report is at a classroom level and presents results as anonymized averages. The teacher data includes a categorical graphical representation (“low”, “average”, “high”) of self-regulation, intelligence, self-efficacy, resilience, depression, trauma, loneliness, altruism, and language development levels in the classroom, with clarifying depictions of these qualities and guidance for their interpretation written by clinical psychologists working in the research project. The school health service report involves individual student data. Upon request, and with the permission of the parents, the multi-professional student welfare body is offered detailed data on the individual’s results on the screening battery. This includes a graphical summary of cognitive, social, and mental health data gathered in the study compared to subsample means (refugee, immigrant, native Finnish) for each child on each variable. The individual results can also be discussed with the child him/herself.

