To test Hypothesis 3, screening battery effects on cognitive, social, and mental health functioning will be evaluated using repeated measures ANOVAs with 2 × 3 for {T_1_, T_2_} and {children who received SB-based support, children who received non-SB-based support, children who did not receive SB-based support} among children who scored above/under critical thresholds, and following up with *t*-tests to compare means. Differences in SB-based actions will also be evaluated qualitatively. We will further use linear regression to test whether changes in mental health (trauma- and depressive symptoms) and social functioning associate with changes in cognitive functioning from T_1_ to T_2_. In addition to analyses in the whole sample, we will also do these analyses by subgroup, separately for our three groups. Classroom atmosphere, teacher self-efficacy and awareness of culturally responsive education, family functioning, child language and development as well as children’s cultural background will be used as covariates in the regression analyses and ANOVAs. Effect sizes and confidence intervals will be reported for main effects and p-value based inference will be de-emphasized based on guidelines for New Statistics [60].

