## Discussion

To be effective in targeting academic underachievement, supportive actions at schools should be based on both scientific evidence about what lies behind such underachievement in general and on specific personalized information about what the student in question needs. This study aims to provide evidence and increase our understanding of both factors. More specifically, it will provide information on the extent to which a standardized screening battery gathering information on cognitive, social, and mental health factors from multiple sources can inform and help plan supportive actions, and whether supportive actions based on the findings of such a battery in turn lead to positive cognitive, social, or mental health outcomes.

The findings and the developed screening battery, intended to stay in use after the research project finishes and spread more widely, may be useful for all children but could be especially valuable for children of immigrant and refugee background, among whom the precise factors underlying academic underachievement remain unclear.

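### Hypothesis 3 is tested on T1–T2 change in children selected for extreme T1 scores, without T1 adjustment, so regression to the mean may be mistaken for an effect of support

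*Protocol article*

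**What the plan says.** Hypothesis 3 (Protocol article, Research question) is comparative and worded as an effect: "that supportive actions informed by the findings of the screening battery have a stronger positive effect than other actions".

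The Analysis plan states that screening battery (SB) effects "will be evaluated using repeated measures ANOVAs with 2 × 3 for" the two time points and three groups: "children who received SB-based support, children who received non-SB-based support, children who did not receive SB-based support". The analysis is restricted to children beyond thresholds, "among children who scored above/under critical thresholds, and following up with" t-tests of means. The Research question section places those thresholds on the SB report and looks at support given afterwards: "We will look at whether children who scored above/under critical thresholds on our Screening Battery (SB) report receive supportive actions during the school year". Selection is therefore on the T1 measurement.

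Support is planned by the school (Aims and objectives). Individual results are released on a further condition (Feedback tool): "Upon request, and with the permission of the parents, the multi-professional student welfare body is offered detailed data".

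The covariates named for the ANOVAs and regressions cover the classroom, the teacher, the family, the child's language and development, and cultural background. No T1 score or other severity measure is named. Control for life changes during the year is promised in Aims and objectives and in Research question, but is not in that list. The same paragraph says that effect sizes and confidence intervals will be given for main effects.

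**The concern.** With two time points, the group × time term compares mean change between groups. Three features meet here: the children are selected on a noisy T1 score, support is not allocated at random, and T1 is not adjusted for.

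Selection alone produces apparent improvement over time. If the support groups also differ in T1 severity, part of that improvement enters the group contrast. Hypothesis 3 is the only one of the three numbered hypotheses about the effect of support, and the Discussion says the battery is meant to remain in use and spread. An artefact read as benefit could therefore support wider use.

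**Working it through.** **The plan's own figure.** The article gives no number for the H3 analysis itself. Its sample size serves only as a yardstick, and it reproduces. For d = 0.5, 80% power and two-sided alpha 0.05 (sidedness assumed), 63 independent children per group are needed. The design effect is 1 + ((1 + 10/17²) × 17 − 1) × 0.07 = 2.161, and 63 × 2.161 = 136.2. Rounded up to whole clusters of 17, this is 9 × 17 = 153, against about 150 stated. That figure is not in dispute.

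**Assumptions, not in the documents.** Scores are standardised and bivariate normal, with T1–T2 correlation r = 0.6–0.8. The worst 20% or 33% are flagged on the outcome being analysed. The true effect of support is zero.

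**Step 1: change over time in the selected children.** Mean T1 distance from the population mean is φ(c)/q, where q is the share flagged and c the cut-off. Expected change towards the mean is (1−r) times this distance.

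| Share flagged | Mean T1 distance | r = 0.6 | r = 0.8 |
|---|---|---|---|
| 20% | 1.400 SD | 0.4 × 1.400 = 0.56 | 0.2 × 1.400 = 0.28 |
| 33% | 1.091 SD | 0.4 × 1.091 = 0.44 | 0.2 × 1.091 = 0.22 |

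The spurious time effect is thus 0.22–0.56 SD, and its upper end exceeds the d = 0.5 used for sample size.

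**Step 2: the group × time contrast.** All groups pass the same threshold. If they have the same mean T1, the common shift cancels and the contrast is unbiased. If support depends on the observed T1 score, the bias is (1−r) × the T1 gap.

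To size the gap, suppose SB-based support reaches 60% of the more severe half of the flagged children and 20% of the other half (assumed). The severe half then makes up 0.6/(0.6 + 0.2) = 0.75 of the supported children and 0.4/(0.4 + 0.8) = 0.333 of the rest, a difference of 0.417.

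- 20% flagged: the halves average 1.755 and 1.045 SD from the mean. Gap = 0.417 × 0.710 = 0.296. Bias = 0.059 (r = 0.8) to 0.118 (r = 0.6).
- 33% flagged: the halves average 1.499 and 0.682. Gap = 0.417 × 0.817 = 0.340. Bias = 0.068 to 0.136.

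The spurious advantage for SB-based support is about 0.06–0.14 SD. In simulation of the same setting, the T1-adjusted difference is within 0.004 SD of zero.

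**Step 3: support that follows something else.** Keep the same setting, but let the 60% v 20% split depend on the child's underlying level, as it might if staff act on what they already know. The change contrast then runs against SB-based support by 0.14–0.23 SD. The T1-adjusted contrast also runs against it, by about 0.2–0.3 SD.

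**Step 4: flagging on another domain.** The article does not say that thresholds are specific to each outcome. If a child is flagged on a different domain, correlated 0.3 with the outcome at the same time point and 0.3r across time (assumed), the Step 2 bias is multiplied by 0.3, giving about 0.02–0.04 SD.

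Steps 2–4 use two groups. The article's third group, as worded, also contains its second, so a calculation on all three would need a definition that is not given.

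**The case against.** A reader might infer that regression to the mean will be reported as an effect of SB-based support, and that the bias favours Hypothesis 3. The documents do not support either. The three groups share one selection rule, so the shared shift cancels unless T1 severity differs. Nothing says that a child's own score triggers support. Individual reports go out on request with parental permission, teachers see only anonymised class averages, and whether flagged children receive support at all is itself a study question. Hypothesis 3 compares SB-informed with other actions, and the most visibly affected children may get the other kind. Step 3 shows that the sign can reverse. This objection stands.

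A reader might also take the follow-up t-tests to be T1 v T2 tests within groups. The article says only that means are compared, and uses similar wording for between-group tests under Hypothesis 1. The main effects to be reported could likewise mean the principal results rather than ANOVA main effects. Within-group and time effects are therefore a permitted reading, not a stated plan.

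The Discussion says the study will inform "whether supportive actions based on the findings of such a battery in turn lead to positive cognitive, social, or mental health outcomes". That is an aim, not a claimed result, though its wording is causal.

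Finally, this is a condensed article, preregistration is still to come, and the covariate list may be incomplete, since it omits the promised life changes. That softens the omission of T1. It does not remove it, because the article itself fixes the model, population, groups and covariates, and control for life changes is not adjustment for T1.

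**Conclusion.** The concern holds as a risk of misreading, not as a certain bias in favour of SB-based support. As stated, the H3 analysis does not separate regression to the mean from an effect of support.

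- The time main effect, or any within-group T1–T2 comparison, would show 0.22–0.56 SD of improvement with no true effect.
- The group × time contrast is biased by (1−r) × any T1 gap if support follows the observed score: about 0.06–0.14 SD under the 60% v 20% split. It is unbiased with equal T1 severity and can be biased the other way.

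These sizes rest on the assumed r, share flagged and split, and on flagging by the analysed outcome. They are smaller if flagging is on another domain. Adjustment for T1 is the better default, but it is not a demonstrated cure: it removes the bias only where support depends on the observed T1 score.

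**What to change.** 1. Make the H3 estimate the between-group difference in the T2 score, adjusted for the T1 score of the same outcome, the covariates already named in the Analysis plan, and the life changes promised in Aims and objectives and in Research question.
2. State that the time main effect and within-group change in threshold-selected children will not be interpreted as benefit.
3. Report H3 as an adjusted association. State that confounding remains from other reasons for receiving SB-based or other support, including who asked for and permitted individual reports and what staff already knew of the child.

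T1 scores are already collected, so only the analysis and wording change, and this can be done before preregistration. Adding the T1 scores of every other domain is not required and would not be free: 20–33% of 450 is only about 90–150 flagged children across three groups. The main cost is a more modest claim about what SB-based support achieves.

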#### Analysis plan

**Power.** In order to form profiles across different groups of children and to assess changes in cognitive, social, and mental health functions across those children who will receive SB based supportive actions and those who do not, we performed a preliminary power analysis to determine the sample size required to detect medium-sized or larger effects on these primary outcomes. Based on typical sizes of Finnish preparatory classes, we estimated the average size of each cluster to be 17, with a variance of 10. Intraclass coefficients for these outcomes are challenging to estimate, but based on our previous cluster-randomized research among war-affected children, values of 0.01–0.1 could be reasonable. With a relatively conservative estimate of 0.07 for the ICC, and setting alpha at 0.05, to achieve 80% power to detect a medium-sized (d = 0.5) or larger effect, we would need about 150 children in each group, meaning approximately 450 children in total.

**Analyses.** Means, standard deviations, and correlations will be evaluated for all variables reported by children, parents, and teachers. To test Hypothesis 1, baseline differences between the study’s three groups will be investigated using 3-way ANOVAs and followed up with *t*-tests to compare means. To test Hypothesis 2, correlation analyses will first be used to examine whether mental health (trauma-related and depressive symptoms) is associated with poorer cognitive function and social competence. Latent profile analyses (using the TidyLPA package in R) will then be run for the entire sample under each of the three dimensions: cognitive, social, and mental health. Emerging profiles will be compared with how they line up with our three groups (refugee, immigrant, native-born Finnish).

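### The plan asks whether the effect of support differs between refugee, immigrant and native-born children, but states no estimate or test of that difference

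*Protocol article*

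**What the plan says.** The Research question section, after asking whether supportive actions are reflected in refugee children's functioning, adds: "We will investigate whether this effect is different compared to non-refugee immigrant children and/or native-born Finnish children". This is a question about a difference between effects.

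The Analysis plan gives one analysis of the support effect. It will be "evaluated using repeated measures ANOVAs with 2 × 3 for" time (T1, T2) and a three-level support factor: "children who received SB-based support, children who received non-SB-based support, children who did not receive SB-based support". The analysis set is restricted to those "among children who scored above/under critical thresholds", with t-tests to follow. The three background groups enter this way: "In addition to analyses in the whole sample, we will also do these analyses by subgroup, separately for our three groups".

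Three other statements bear on the point:

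- Children's "cultural background will be used as covariates in the regression analyses and ANOVAs". No product term with support is mentioned.
- "Effect sizes and confidence intervals will be reported for main effects", while inference from p-values is to be played down.
- Background group is named as an ANOVA comparison only for Hypothesis 1, where "baseline differences between the study’s three groups will be investigated using 3-way ANOVAs".

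**The concern.** The three levels in the 2 × 3 design are support categories, not background groups. The model therefore gives one support effect for the whole sample, and the repeated analyses give one for each group. None of these outputs is the difference between the effect in refugee children and the effect in another group.

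A reader given three separate estimates will compare them by eye. Small subgroups scatter by chance, so an apparent contrast (support seems to help one group and not another) can arise when the true effect is the same in all three. The uncertainty of the contrast is larger than that of either estimate, and the separate analyses do not show it. The Discussion suggests that the battery may be especially valuable for immigrant and refugee children, so a contrast of this kind is likely to be noticed and quoted.

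**Working it through.** **1. Question against method.**

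| Element | Where stated | Does it give the difference in support effect between groups? |
|---|---|---|
| Time × support ANOVA, whole sample | Analysis plan | No, one common effect |
| The same analyses within each group | Analysis plan | No, three effects without a contrast |
| Cultural background as covariate | Analysis plan | No. Without a product term with support, the support effect cannot vary by background. The covariate is also not said to be the refugee/immigrant/native-born classification |
| 3-way ANOVAs by group | Analysis plan, Hypothesis 1 | No, baseline only |
| Latent profiles lined up with groups | Analysis plan, Hypothesis 2 | No, not about support |

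**2. The plan's own sample size.** Inputs from the Power paragraph: d = 0.5, alpha 0.05 (two-sided assumed), 80% power, ICC 0.07, mean cluster size 17, variance 10.

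- Unclustered n per group = 2 × ((1.96 + 0.842)/0.5)² = 62.8, so 63.
- Design effect, equal clusters: 1 + 16 × 0.07 = 2.12, and 63 × 2.12 = 134.
- Design effect, unequal clusters: CV² = 10/17² = 0.0346, so 1 + (1.0346 × 17 − 1) × 0.07 = 2.16, and 63 × 2.16 = 136.
- With a t-test on cluster degrees of freedom and equal clusters, 9 clusters of 17 = 153 per group gives 80.5% power. At exactly 150 the power is 79.6% (equal clusters) or 78.8% (unequal).

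The stated figure of about 150 per group therefore reproduces. It is a sample size for comparing two groups, not for comparing two effects.

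**3. Precision of the missing contrast.** Assumptions, because the article gives neither figure: a share f of each group's 150 children crosses the thresholds, and these split equally over the three support categories. The analysed score has SD 1, and the test is two-sided at 0.05.

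- Effective cell size: m = 150 × f / 3 / DE, where DE is the design effect.
- Support effect within one group: SE = √(2/m).
- Difference between two groups' effects, taken as independent: SE = √(4/m), which is √2 = 1.41 times as large.
- Power for a 0.5 SD difference = Φ(0.5/SE − 1.96). Detectable difference at 80% power = 2.80 × SE.

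| f | DE | m | Power for 0.5 SD | Detectable difference (SD) |
|---|---|---|---|---|
| 100% | 1 | 50.0 | 42% | 0.79 |
| 100% | 2.16 | 23.1 | 22% | 1.16 |
| 50% | 1 | 25.0 | 24% | 1.12 |
| 50% | 2.16 | 11.6 | 13% | 1.65 |
| 30% | 1 | 15.0 | 16% | 1.45 |
| 30% | 2.16 | 6.9 | 10% | 2.13 |

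One example in full: f = 100%, DE = 1 gives SE = √(4/50) = 0.283 and power Φ(1.768 − 1.96) = Φ(−0.19) = 42%.

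The rows with DE 2.16 carry the design effect for full classes over to the flagged children. Fewer flagged children per class would lower it, so these rows are pessimistic. The T1–T2 correlation and an unequal support split would also move the figures.

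**4. Subtracting the separate estimates.** The Participants and procedure section draws one preparatory and one regular class per school, and places all asylum seekers and most non-refugee immigrants in preparatory classes for their first year. Refugee and immigrant children will therefore often share a class. Their separate estimates are not independent, and a subtraction that treats them as independent gets the standard error wrong. A joint model with a class term avoids this.

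**The case against.** Several points can fairly be made for the plan.

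- *Whole-sample analyses are run too.* They are, but they contain no term that lets the support effect vary by background.
- *Background is adjusted for.* A reader might infer that the whole-sample models ignore background. The document does not support that, since cultural background is a listed covariate. What remains open is whether this covariate is the three-group classification.
- *Background may confound the support comparison.* A reader might assume that background alters both the chance of receiving battery-based support and the rate of change. The article poses these as questions and does not assert them, so this is a possibility only.
- *The plan favours estimation over p-values.* A reader might infer that the authors will declare a difference when one group is significant and another is not. Nothing says so. A reader might also attach a rate of conflicting results to the design. With power p in each of three independent groups and the same true effect, the chance that they do not all agree on significance is 1 − p³ − (1 − p)³: 27% at p = 10%, 63% at 30%, 75% at 50% and 48% at 80%. This depends on an unknown p, on an independence that shared classes break, and on a significance reading that the plan plays down. It illustrates the hazard and does not measure it. An estimation approach still needs the estimate and interval for the difference, which are what is missing.
- *Main effects may be meant loosely, as the principal results.* That is possible, but the between-group difference is not named on that reading either.
- *This is not a numbered hypothesis.* Correct: Hypothesis 3 compares battery-informed with other actions. The question is secondary, but the article says it will be investigated.
- *An article condenses the full plan.* Here it does not stay silent. It names a method for the three groups, and that method does not answer the question.

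**Conclusion.** The point holds in this form: for the question whether the support effect differs by background, the three groups are handled only by repeating the analyses within each group, and no between-group contrast is stated. This follows from the text and does not depend on any sample size assumption.

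Its size is limited. Hypothesis 3 itself is not affected. Under the assumptions in the working, power for a 0.5 SD difference in effect is about 10% to 42%, so the gain from the correct analysis is an honest, wide interval in place of an informal comparison of three estimates. It should be corrected before the analysis is fixed.

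**What to change.** In all children beyond the critical thresholds, fit one model that adds background group and the time × support × background interaction to the planned analysis, with an allowance for class clustering. Report the differences in support effect, refugee minus immigrant and refugee minus native-born, with 95% confidence intervals as the answer to the research question. Label them exploratory, and keep the separate group results as description.

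The repeated measures framework need not be replaced. A support × background term in a model of the T2 score adjusted for T1 addresses the same question, but the two forms can give different estimates when groups differ at baseline, so one should be named in advance.

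Also state that the refugee/immigrant/native-born grouping enters the whole-sample Hypothesis 3 and change-regression models, whether as the cultural background covariate or beside it.

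The cost is analysis wording, with no further data collection. Two limits should be stated with the result: the intervals will be wide, and the refugee versus native-born contrast partly reflects preparatory versus regular class, which the model cannot fully separate.

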In sum, we need to understand the interplay of children’s cognitive, social, and mental health functions to offer targeted and tailored help for children at schools. This is important for all children, but would also benefit immigrant and especially refugee children, for whom uncovering the challenges underlying school performance has for a long time been seen as challenging. Our project develops a research based, validated and universal tool, the Screening Battery (SB), for evaluating and supporting further action toward better cognitive, social, and mental health functions. In this project, we develop, pilot and implement this tool in Finnish schools, and collect groundbreaking data on the interplay of cognitive, emotional, and social mechanisms that may underlie school problems among refugee children. We will compare profiles between refugee children and non-refugee immigrant children as well as their native peers in these dimensions. We will also study the effectiveness of supportive actions informed by the results of the screening battery, and planned by the school, while controlling for other significant life changes over the study year.

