### Tests and measures

**Demographic variables.** At T_1_, we ask the children, as well as their parents, about the children’s age, class, gender, living arrangements, and country of birth. If the country of birth is not Finland, we ask how many years they have spent in Finland, with whom they came to Finland, immigration status, place of residence, and reason for migration. At T_2_, we ask about significant life changes after T_1_, including changes in legal status in host country, family composition, significant losses or other changes in close relations, and other significant life changes. The same kind of questionnaire was used in a previous study among refugee and native-born children in Finland [10, 33]. At T_2_, we collect a list of supportive actions the child thinks they have received during the school year.

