#### Parental report

**Demographic variables.** At T_1_, we ask background information such as parents’ age, country of birth, education, marital status, and housing arrangements are collected. We also ask parents to report on the child’s country of birth, current legal status in host country, time in host country, and reason of migration. We request this information from both parents and children. Parents would be more reliable informants on these questions, but in the likely situation that we are unable to reach all parents, we will have the child’s report on the same topics. If there is discrepancy in child and parent reports, we rely on parents’ report. At T_2_, we ask about significant life changes after T_1_. The questionnaire includes changes in legal status in host country, family composition, significant losses, or other changes in close relations and other significant life changes. At T_2_, we collect information on whether or not the information provided by the SB has been used for the child, and a list of supportive actions the child or family has received.

**Family functioning** is measured by 12 items from the General Functioning subscale of the McMaster Family Assessment Device (FAD) [54, 55]. The parent assesses on a four-point scale how much they agree with the descriptions of family functioning (0 = s*trongly agree*, 1 = a*gree*, 2 = d*isagree*, 3 = s*trongly disagree*).

**Child language and development** is measured by 10 selected items from the Alberta Language and Development Questionnaire (ALDeQ) [56]. The selected items were chosen to reflect the parents’ view of the general development of the child and possible challenges in it, as well as parents’ own reading or learning difficulties. The parent evaluates each item on a four-point scale, but due to the varying form of the items, the answer categories vary between items (such as 0 = *never*, 1 = *rarely*, 2 = *sometimes*, 3 = *very much* or 3 = *very easy*, 2 = *easy enough*, 1 = *sometimes not easy*, 0 = *no, very hard*).

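### The covariates named for the supportive-action analyses omit the significant life changes that the aims and the research question say will be controlled for

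*Protocol article*

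**What the plan says.** The protocol article commits to this adjustment twice. Under Aims and objectives, the effectiveness of supportive actions is to be studied "while controlling for other significant life changes over the study year". Under Research question, in the paragraph that leads to Hypothesis 3, the effect on the child's functioning is to be examined "after controlling for other significant life changes during the study year".

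The data are collected from two informants at T2. For the child, Tests and measures states: "we ask about significant life changes after T_1_, including changes in legal status in host country, family composition, significant losses". For the parent, Parental report states: "The questionnaire includes changes in legal status in host country, family composition, significant losses, or other changes in close relations".

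Under Analysis plan, Hypothesis 3 is tested as follows: "screening battery effects on cognitive, social, and mental health functioning will be evaluated using repeated measures ANOVAs with 2 × 3". The three levels of the second factor are defined by the kind of support received, among children beyond critical thresholds on the battery. The covariates are then itemised: "Classroom atmosphere, teacher self-efficacy and awareness of culturally responsive education, family functioning, child language and development". The same sentence adds the child's cultural background and applies the list to both the regressions and the ANOVAs. Life changes appear nowhere in the Analysis plan.

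**The concern.** The aims and research question describe an effect adjusted for life changes. The Analysis plan, applied as it stands, would give an effect not adjusted for them.

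This matters because the article describes no random allocation to the kinds of support. An event during the year, such as a loss or a change in legal status, could plausibly lead a school to act and could also move depression or trauma scores. The document does not state either link, but its promise to control for such events shows that the authors saw the risk. If the variable is left out, a difference between support groups could partly reflect what happened to the children and not the support. The same applies to the comparison of the effect between refugee, non-refugee immigrant and native-born children.

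The study is to be preregistered. If the covariate set is unsettled at that stage, the choice to adjust or not stays open until results are known.

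**Working it through.** The article gives no figure on this point, so there is none to reproduce. The check sets the sections side by side.

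1. **Is the control promised?** Yes, in two places: Aims and objectives, and Research question. Both attach it to the effect of supportive actions.
2. **Is the variable measured?** Yes, at T2 in two places: by the child (Tests and measures) and by the parent (Parental report).
3. **Is it among the named covariates?** No. The six are classroom atmosphere, teacher self-efficacy, awareness of culturally responsive education, family functioning, child language and development, and cultural background.
4. **Does one of the six stand in for it?** No. Family functioning is a parent-rated scale of how the family works in general. Child language and development is a parent's view of development and learning difficulties. Cultural background is not an event during the year. The other three describe the teacher or the classroom. None records a change in legal status or a loss between T1 and T2.
5. **Is the Hypothesis 3 contrast protected in another way?** Not by design: group membership follows from support received, with no randomisation described.
6. **Can the bias be sized?** To a first approximation, for an any-change indicator:

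   bias = (difference between support groups in the share of children with a life change) × (effect of a life change on the outcome, in SD)

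   The document gives neither term. The sign is also unknown, since life changes can be for better or worse.
7. **Does the promise reach the regression of cognitive change on change in mental health and social functioning?** No. The sentence under Research question that introduces that analysis carries no such condition.

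**The case against.** The strongest reply is that the covariate sentence is silent, not contradictory. It does not say that only these variables will be used. It is worded for all the ANOVAs, including the baseline comparisons for Hypothesis 1, where a variable measured at T2 could not sensibly enter. A general list of that kind can be read together with the specific commitment under Research question. The article is also condensed, and the coding of a multi-item questionnaire may well be left to a fuller plan.

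Part of this stands. The list is not expressly closed, and the article nowhere says that life changes will go uncontrolled. But the article does not defer its covariates. It itemises six and says which models they enter, while the only adjustment variable named in the aims and research question is missing. Condensing the text does not readily explain that.

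Three stronger readings are tempting, and the document supports none of them:

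- **That the bias has a known size.** Assuming a 20 to 40 percentage-point difference in life changes between support groups and an effect of 0.3 to 0.5 SD gives 0.20 × 0.3 = 0.06 SD to 0.40 × 0.5 = 0.20 SD. Both inputs are invented, and the product ignores overlap with covariates already in the model. It says nothing about this study.
- **That the change-on-change regression breaks the same promise.** The promise does not extend to it.
- **That life changes fall mainly on refugee children.** This is plausible, but nowhere stated.

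**Conclusion.** The point holds as an inconsistency within the article. Control for life changes is promised twice and the data are collected from two informants, yet the variable has no stated place in the analysis that needs it. The comparison at risk is Hypothesis 3, including its by-group analyses, because its groups are not randomised.

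The textual omission is certain. That it would bias the result rests on an assumption: that life changes relate both to the support received and to the outcomes. The amount and direction of any bias cannot be obtained from the document. The change should be made before preregistration, but the point does not by itself undermine the study.

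**What to change.** In the Analysis plan, add significant life changes between T1 and T2 as a covariate in the Hypothesis 3 supportive-action models, in the whole sample and in the by-group analyses. Four details should be settled in the same edit:

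- **Coding.** An any-change indicator or a count from the existing questionnaire is enough. A split into adverse and positive changes would need a new coding rule, because no such rating is described.
- **Informant.** State which report is used when child and parent differ or one is missing. The existing preference for the parent's report is given for background and migration items, so it should be extended explicitly if it is wanted here.
- **Model form.** In the repeated measures ANOVA, enter the covariate with its interaction with time. As a between-child term alone it would not adjust the difference in change between support groups.
- **Reporting.** Give the Hypothesis 3 results with and without the covariate. It is measured after baseline and could partly follow from support, since the parent is also asked about support given to the family.

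Adding it to the regression of cognitive change on changes in mental health and social functioning is optional. If the authors prefer not to adjust, they should withdraw the commitment in the aims and research question and say why.

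The cost is a short addition to the text, one more covariate (with its time interaction) and a second set of estimates. No new data are needed.
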